# Chemotherapy in conjunction with traditional Chinese medicine for survival of patients with early female breast cancer: protocol for a non-randomized, single center prospective cohort study

**DOI:** 10.1186/s13063-019-3848-8

**Published:** 2019-12-17

**Keywords:** Traditional Chinese medicine, Quality of life, Study design, Disease-free survival, Breast cancer

## Abstract

**Background:**

Chemotherapy after surgery for breast cancer plays a fundamental role in reducing the risk of distant and local recurrence. An increasing number of patients seek traditional Chinese medicine (TCM) during adjuvant chemotherapy to relieve symptom discomfort and side effects as well as to strengthen the body’s defenses. However, evidence on how concurrent TCM treatment affects prognosis is scarce. This trial aims to evaluate the association between TCM treatment and disease-free survival outcomes for patients with early breast cancer who are undergoing adjuvant chemotherapy.

**Methods/design:**

This is a non-randomized, single center, prospective cohort study begun in November 2018 in Kaohsiung, Taiwan. A sample of 310 participants diagnosed with early breast cancer was recruited from the Breast Cancer Research Team and will be followed up every 3 to 6 months until October 2023. Detailed information of the participants, including general information, history of cancer, quality of life, side effects and safety of treatment, TCM body constitution, and meridian energy analysis, was collected face to face at baseline.

**Discussion:**

This is the first prospective observational cohort study on TCM in patients with early breast cancer who are receiving adjuvant chemotherapy to evaluate the prognosis. Through this trial, we hope to assess the feasibility of a larger-scale clinical trial in the future and formulate an integrated TCM care program.

**Trial registration:**

ClinicalTrials.gov, NCT03797248. Registered on 5 January 2019.

## Background

Breast cancer is the most common cancer in women, accounting for 25.1% of all cancers worldwide [1]. Breast cancer has been the fastest-growing incidence of cancer in Taiwan over the past 10 years, with a growth rate approaching 58% and an incidence of 188–194 per 100,000 women-years [2].

Chemotherapy plays an important role in the systemic treatment of breast cancer, and it is the cornerstone of therapy for patients who are not candidates for hormone therapy [3]. An Early Breast Cancer Trialists’ Collaborative Group (EBCTCG) meta-analysis study reported that taxane-based or anthracycline-based chemotherapy may decrease cancer recurrence and mortality, largely independent of age, lymph node metastasis, or estrogen receptor status [4]. Currently, after breast surgery, National Comprehensive Cancer Network (NCCN) guidelines specify only adjuvant chemotherapy to eliminate remaining cancer cells and improve survival in most patients with early stage breast cancer [5, 6]. Besides killing cancer cells, chemotherapeutic agents can also damage healthy tissues, leading to side effects that negatively affect patients’ quality of life (QOL) and compliance with cancer treatment [7]. Therefore, there is a clinical need to find an intervention to manage the discomfort of chemotherapy and improve patients’ tolerance and well-being.

Increasing numbers of patients use a wide range of complementary and alternative medicine (CAM) therapies, including herbs, vitamins, homeopathic remedies, and Chinese herbal medicines (CHMs), during their anticancer treatment. The use of CHMs based on traditional Chinese medicine (TCM) theory for breast cancer has been recorded in ancient Chinese books for more than 2000 years. In Taiwan, nearly 20% of patients seek CHM as part of the treatment for their breast cancer [8]. As a CAM therapy for breast cancer, CHM has gradually shown its effects in controlling the progression, increasing the susceptibility to radiotherapy and chemotherapy, elevating immunity, and decreasing the toxicities or side effects of cancer therapies [9]. Authors of a systematic review demonstrated that the combined use of CHM with chemotherapy was an appropriate adjunctive therapy for immediate tumor response and chemotherapy-induced toxicities [10], but the supporting evidence was insufficient because most of the randomized controlled trials (RCTs) had poor study design. In addition, it is unproven whether combined CHM therapy is more effective than the standard adjuvant chemotherapy for clinical prognosis, especially in early breast cancer. Therefore, we planned to perform a single center prospective cohort trial to investigate whether the intervention of CHM can improve the prognosis of postoperative breast cancer patients in terms of disease-free survival (DFS), and then to provide evidence that TCM treatment is effective and safe. Meanwhile, this study can provide a breast cancer patient information database, which may correct the guidelines for TCM treatment, build trust between Western medicine doctors and TCM practitioners, and enhance the role of TCM in integrated medical care.

## Methods/design

### Study design

This study is a non-randomized, single center, prospective cohort study. The study began in November 2018 and is currently ongoing. A cohort of 310 patients aged more than 20 years with breast cancer with histologically diagnosed stages 1–3 after partial or radical surgery were enrolled from an academic medical center. All participants will complete six to eight cycles of adjuvant chemotherapy, which may last 6 months. The standard chemotherapy regimens include anthracycline-, taxane-, or anthracycline plus taxane-based chemotherapy specified by the NCCN guidelines, based on their disease states. At the time the participants enter the study, the time between surgery and initial chemotherapy is not more than 1 month. The study consists of two stages. Stage I is a cross-sectional study at baseline, and stage II is a cohort study across 3 years of follow-up. Participants will be followed up every 3 to 6 months for 3 years, until recurrence or death. The feasibility and precision of the entire process will be overseen by two supervisors. To ensure that patients adhere to the follow-up schedule, we remind patients of their scheduled visits by telephone or text message. Additionally, incentives are used to express appreciation for the participants’ recruitment and retention throughout the years.

### Study settings and participants

The study is being performed in Kaohsiung Chang Gung Memorial Hospital (KCGMH) in Taiwan. Approximately 2–4 weeks after the completion of surgery, the early breast cancer patients are hospitalized for port-a-catheter implantation and administration of the first cycle of adjuvant chemotherapy. At that time, we are referred to the patients by the Breast Cancer Research Team on the day of their hospitalization. Participant screening is implemented by our department specialists with a background in oncology. For eligible patients, the researcher provides details on the purpose, specific content, instructions on how to complete the trial, and precautions of cancer treatment. After we obtain their informed consent, patients are enrolled in the study.

During the period of adjuvant chemotherapy, the participants can decide whether to accept the CHM intervention based on their personal conditions and evaluation of their own physiques. If a patient is willing to see TCM practitioners, we arrange CHM treatment for her. However, participants treated with CHM need to receive such treatment for at least half of the whole period. Participants taking CHM during the period of adjuvant chemotherapy are referred to as cohort 1, and patients receiving only chemotherapy without CHM belong to cohort 2. CHM is prescribed by TCM practitioners with more than 5 years of experience according to the TCM Treatment for Breast Cancer protocol developed in our Integrative Cancer Center (Table 1). The protocol and consensus assessment used in the study are based on the integration of empirical data and previous research of TCM syndromes in breast cancer [11, 12]. We record the number of TCM clinic visits, common CHM prescriptions, and days of taking the medicine, but we do not interfere with the treatment of TCM practitioners. The study project and estimated recruitment numbers are presented in Fig. 1.

**Table 1 Tab1:** Syndrome differentiation-based CHM treatments for patients with breast cancer during adjuvant chemotherapy period

Pattern type	Symptoms	Treatment principle	Prescriptions (components)
肝鬱氣滯 Stagnation of liver-*qi*	Depressive mood and other irritability, feeling wired or having mood swings, distension in the upper abdomen, or a sense of constriction in the chest, poor vision, bitter taste, dry throat, vexation and irritability, and strong pulse	Relieving *qi* stagnancy in liver	Chai Hu Shu Gan Tang 柴胡疏肝湯 (*Pericarpium (Per.) Citri Reticulatae*, *Radix (Rx.) Bupleuri*, *Rhizoma (Rz.) Chuanxiong*, *Fructus (Fr.) Aurantii*, *Rx. Paeoniae Alba, fried Rx. Glycyrrhizae, Rz. Cyperi*) or Xiao Yao San 逍遙散 (*Rx. Bupleuri*, *Rx. Angelicae Sinensis*, *Rx. Paeoniae Alba*, *Rz. Atractylodis Macrocephalae*, *Poria*, *Rx. Glycyrrhizae Preparata*, *Herba (Hb.) Menthae Haplocalycis*, *Rz. Zingiberis Recens*)
脾虛痰濕 Spleen deficiency with phlegm dampness	Feeling heavy and tired, poor appetite, abdominal distension, diarrhea, nausea, vomiting, dyspepsia, a plump greasy tongue, and soft pulse	Tonifying the spleen and removing dampness	Liu Jun Zi Tang 六君子湯 (*Rx. Ginseng*, *Rz. Atractylodis Macrocephalae*, *Poria*, *Fried Rx. Glycyrrhizae*, *Per. Citri Reticulatae*, *Rz. Pinelliae Preparatum*) or Wei Ling Tang 胃苓湯 (*Rz. Alismatis*, *Poria*, *Polyporus*, *Rz. Atractylodis Macrocephalae*, *Ramulus (Ram.) Cinnamomi*, *Rz. Atractylodis*, *Cortex (Cx.) Magnoliae Officinalis*, *Per. Citri Reticulatae*, *Rx. Glycyrrhizae Preparata*, *Rz. Zingiberis Recens*, *Fr. Zizyphi Jujubae*)
肝腎陰虛 Deficiencies of liver- and kidney-yin	Feeling annoyingly hot in chest area and in palms of hands and feet, hypochondriacal pain, back pain, blurred vision, dizziness, tinnitus, night sweats, red tongue with scanty fur, thin and rapid pulse	Nourishing yin of liver and kidney	Liu Wei Di Huang Wan 六味地黃丸 (*Rx. Rehmanniae Preparata*, *Fr. Corni Shan*, *Rx. Dioscoreae*, *Poria*, *Cx. Moutan*, *Rz. Alismatis*) and Er Zhi Wan 二至丸 (*Fr. Ligustri Lucidi*, *Hb. Ecliptae*)
痰(瘀)熱夾雜 Stagnation of heat and phlegm (or stasis)	Hard, swelling, or painful lump in the breast, extreme heat, thirst, bitter taste, headache, dark red tongue with a yellow coat, slippery and rapid pulse	Cleaning heat and reducing toxicity, removing the sludge, and eliminating the swelling	Huang Lian Wen Dan Tang 黃連溫膽湯 (*Caulis Bambusae in Taeniam*, *Fr. Aurantii Immaturus*, *Rz. Pinelliae Preparatum*, *Per. Citri Reticulatae*, *Poria*, *Rx. Glycyrrhizae*, *Fr. Jujubae*, *Rz. Zingiberis Recens*, *Rz. Coptidis*) or Xue Fu Zhu Yu Tang 血府逐瘀湯 (*Semen (Sm.) Persicae*, *Flos Carthami*, *Rx. Angelicae Sinensis*, *Rz. Chuanxiong*, *Rx. Paeoniae Rubra*, *Rx. Cyathulae*, *Rx. Bupleuri*, *Rx. Platycodi*, *Fr. Aurantii*, *Rx. Rehmanniae*, *Rx. Glycyrrhizae*)
氣血兩虛 Deficiencies of *qi* and blood	Paleness, weakness, weak or breathy voice, emotional exhaustion, palpitation, insomnia, cramps, numbness, pale tongue, weak pulse	Invigorating *qi* and enriching the blood	Gui Pi Tang 歸脾湯 (*Rx. Ginseng*, *Rx. Astragali*, *Rz. Atractylodis Macrocephalae*, *Poria*, *Sm. Zizyphi Spinosae*, *Arillus Longan*, *Rx. Aucklandiae*, *fried Rx. Glycyrrhizae*, *Rx. Angelicae Sinensis*, *fried Rx. Polygalae*, *Rx. Zingiberis Recens*, *Fr. Jujubae*)

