### Primary outcome

The primary outcome of this study is 3-year DFS, defined as the period after curative treatment when no disease can be detected. This indicator will be calculated at the end of the study. The outcome assessment with regard to survival, local and regional relapse, and distant metastasis will be obtained by either review of the hospital records system or contact by mail or phone. The date of last evaluation will be recorded if patients have neither recurrence nor metastasis unless they reach censored data or there is loss of follow-up.

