### Statistical analysis

All statistical analyses will be performed in SPSS version 17.0 (SPSS Inc., Chicago, IL, USA). Statistical significance will be defined as *P* < 0.05. Based on the data distribution, the measurement data will be analyzed by *t* test or the Mann–Whitney *U* test, and the counting data by the χ^2^ test or Fisher’s exact test. Kaplan–Meier survival analyses will be used with regard to the DFS, and the log-rank test will be used between the two cohort groups. Repeated measures analysis of variance (ANOVA) and linear mixed models will be used to evaluate the repeated measures such as QOL, TCM pattern, and MEAD related to breast cancer and to compare the differences between the two groups. Therapeutic efficiency will be analyzed using the data of the full analysis set (FAS) and per protocol set (PPS); safety evaluation will be based on the data of the safety analysis set (SS) for statistical analysis.

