Some limitations of this study are as follows. First, the study is an observational study, so the evidence level is lower than that of an RCT. TCM treatments are individualistic and dynamic in approach because they are based on clinical signs and symptoms at different stages, so there may not be a standard treatment for a population [27]. Moreover, the difficulties of randomization and blinding, selection of controls, and patient’s willingness and motivation to complete a study are other issues in conducting an RCT [28]. Although incorporating TCM principles in an RCT poses a challenge, we still can employ an evidence-based model for this traditional practice [29]. Second, baseline characteristics between the two cohorts may be imbalanced if the patients tend to choose combined CHM treatment in stage I. To resolve this problem, we will analyze the data by propensity score matching to control for some possible related factors. Third, the evidence supporting our TCM Treatment for Breast Cancer protocol is not sufficient. The protocol was developed in 2016, and it has not since been popularized due to a lack of large-scale clinical research. This will influence the rationality of treatment using this protocol, and our results may not be representative of the whole population. Finally, queue migration and the long time required for follow-up are both challenges in a cohort study. One way to avoid such problems is to strengthen the role of the cancer case manager in effective follow-up of the participants.

This proposal outlines the methodology for an observational study of adjuvant chemotherapy combined with CHM on the prognosis of patients with early breast cancer; the study adheres to the Standard Protocol Items: Recommendations for Interventional Trials (SPIRIT) statement [30]. The SPIRIT checklist is provided as Additional file 1. Results of this study should help provide support and parameters for the use of integrative TCM and anticancer treatments in patients with breast cancer.

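### If the half-period CHM rule defines cohort 1, the log-rank comparison credits that cohort with guaranteed event-free time (about 1 to 2 points of 3-year DFS), and women who take CHM for less than half of the period have no clear cohort

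*Protocol article*

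**What the plan says.** Under Study settings and participants, women are enrolled when admitted for the first chemotherapy cycle. After that, "During the period of adjuvant chemotherapy, the participants can decide whether to accept the CHM intervention". A duration condition follows: "participants treated with CHM need to receive such treatment for at least half of the whole period". The next sentence names the groups. For the CHM group it reads: "Participants taking CHM during the period of adjuvant chemotherapy are referred to as cohort 1". The comparison group is set by the absence of CHM: "patients receiving only chemotherapy without CHM belong to cohort 2".

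On timing, Study design states: "All participants will complete six to eight cycles of adjuvant chemotherapy, which may last 6 months". It also has women followed for 3 years, ending at recurrence or death. Table 2 runs from screening through months 1, 3 and 6 (chemotherapy) to month 36, with imaging and tumour markers at screening and at months 3 and 6. A row for cohort migration is ticked from month 9 on.

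DFS is "defined as the period after curative treatment when no disease can be detected", with no date attached. The 85% benchmark under Sample size calculation is counted after surgery. For the analysis, "the log-rank test will be used between the two cohort groups". The Discussion adds propensity score matching to deal with baseline imbalance.

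**The concern.** Cohort membership appears to depend on something that happens after the DFS clock starts. With chemotherapy of about 6 months, half is about 3 months. A woman who starts CHM at once can qualify at month 3 at the earliest. One who starts at month 3 qualifies only at month 6. A relapse or death before that point prevents her from qualifying. Under that reading cohort 1 cannot have an event in its first 3 to 6 months, while cohort 2 can.

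Kaplan-Meier curves and a log-rank test that treat cohort as fixed from the start count this guaranteed time as CHM benefit. Matching on baseline variables balances who the women were at entry and leaves the condition on later survival in place.

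There is also a problem of assignment. A woman who takes CHM for less than half of the period is in cohort 1 by the naming sentence, outside it by the duration condition, and outside cohort 2 because she has taken CHM. If she is left out, cohort 1 is filtered on a post-baseline event that may be linked to tolerance and prognosis. Cohort 2 has no matching filter.

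**Working it through.** **The plan's own figure.** Inputs from Sample size calculation: 85% against 95%, two-sided α = 0.05, 80% power. With pooled variance, n = [1.960·√(2·0.90·0.10) + 0.842·√(0.85·0.15 + 0.95·0.05)]² / 0.10² = (0.8315 + 0.3521)² / 0.01 = 140.1, so 141 per cohort. This matches the protocol, and 141 × 1.1 = 155.1 gives its 155. The sample size is not in dispute.

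**Is the clock running when membership is decided?**
- For an early clock: Table 2 has one axis to month 36 that includes chemotherapy, imaging at months 3 and 6, follow-up from baseline, and an 85% figure counted after surgery.
- For a later clock: the undated DFS definition, and Table 2's follow-up heading, which begins at month 9.

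The balance favours an early clock, but the text does not settle it.

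**Size of the bias with no CHM effect.** Assumptions: true 3-year DFS of 85% in everyone, constant hazard, cohort 2 unaffected at 85%, the half-period counted on 6 months of chemotherapy, and cohort 1 event-free for its first m months.

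Apparent cohort 1 DFS = 0.85^((36 − m)/36):
- m = 3: 0.85^(33/36) = 86.2%, a gain of 1.2 points
- m = 6: 0.85^(30/36) = 87.3%, a gain of 2.3 points (upper bound, since every cohort 1 woman would have to qualify as late as possible)

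Simulated log-rank tests (8,000 runs, 141 per cohort, no CHM effect):

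| Guaranteed months | Event-rate ratio | False positives favouring CHM | Two-sided false positives |
|---|---|---|---|
| 0 | 1.00 | 2.4% | 4.8% |
| 3 | 0.91 | 4.7% | 6.0% |
| 6 | 0.82 | 9.0% | 9.6% |

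**Short-term users.** The protocol gives neither their number nor their prognosis, so the bias from leaving them out cannot be sized. The loss of power can be shown over an assumed range. If 10%, 20% or 30% of cohort 1 is left out, power falls from 80.3% to 77.7%, 74.4% or 70.4%.

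**Cost of a month-6 landmark.** On the planned rates and a constant hazard, DFS from month 6 to month 36 is 0.85^(30/36) = 87.3% against 0.95^(30/36) = 95.8%. That needs 168 per cohort, and 141 gives 72.9% power. Expected events over 3 years are 141 × (0.15 + 0.05) = 28.2. Those before month 6 are 141 × (0.0267 + 0.0085) = 5.0.

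**The case against.** The strongest reply is that time zero is undated. If curative treatment includes adjuvant chemotherapy, membership is settled when DFS starts and no guaranteed time is counted. That stands as a possibility, so the bias is conditional.

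Second, the naming sentence carries no duration condition. The half-period sentence could be an adherence requirement for the per protocol set, since Statistical analysis plans both a full analysis set and a per protocol set. This also stands. A reader might infer that short-term users are certainly dropped, but the text supports only that its sentences conflict.

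Third, all women are expected to complete chemotherapy, and withdrawal from it ends participation in either cohort. If early failures leave both cohorts this way, the difference shrinks. The protocol does not say that they leave the analysis.

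Three stronger readings are tempting and not supported:
- *A spurious benefit of several points, around half the planned effect.* That would need an assumed share of short-term users with an assumed worse prognosis, neither of which is in the protocol. It could also count early failures twice, once as early events and once as early stoppers.
- *Early failures among CHM starters swelling cohort 2's events.* Cohort 2 is limited to women without CHM. Only women who fail before any CHM would fall there.
- *A contradiction over when CHM is chosen*, because the Discussion speaks of imbalance "if the patients tend to choose combined CHM treatment in stage I". Enrolment coincides with the first cycle, so a choice at the start of chemotherapy is also a baseline choice, and the Discussion sentence is conditional.

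Finally, an analysis plan that is not shown may contain a landmark or a time-dependent model, and the absence of one here is no fault in itself. The point rests on what the article does state: the cohort rule and the test, which do not fit together under the more likely clock.

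**Conclusion.** The concern holds conditionally. If the half-period rule defines cohort 1 and DFS is counted from surgery or the first cycle, the stated comparison favours CHM even when CHM does nothing, and baseline propensity matching does not correct it. On the protocol's 85% and a constant hazard, the effect is about 1.2 points for 3 guaranteed months and at most about 2.3 for 6, against a planned 10. It would be smaller if recurrence is rare in the first months, and absent if DFS starts when chemotherapy ends.

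This could not by itself produce the planned difference. It does raise the chance of a false finding for CHM, from 2.4% to between 4.7% and 9.0% in the simulations.

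The conflict over short-term users exists whichever clock is used. Leaving them out would add selection of unknown size. The meaning of the whole period in the duration condition is not defined and should be fixed at the same time.

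**What to change.** 1. Date DFS time zero identically for all women, for example at the first chemotherapy cycle.
2. Keep every enrolled woman in the full analysis set, including those with short CHM use, and reconcile the cohort sentences so that each woman has one stated place.
3. In the primary DFS model, enter CHM as a time-dependent exposure: unexposed until the first prescription, exposed from then on. Carry the baseline factors meant for propensity matching into that model.
4. Use the half-period definition only in a month-6 landmark analysis among women still event-free, with DFS counted from the landmark.
5. Do not reclassify women by later cohort migration. Examine migration as a time-varying sensitivity analysis.

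No new data are needed, because TCM clinic visits, prescriptions and days of medicine are already recorded. The cost is revised wording, a different model and a changed question: the primary contrast becomes CHM started rather than CHM sustained. The landmark analysis, which keeps the sustained-use question, loses about 5 of about 28 expected events and has about 73% power with 141 per cohort, so it should be supportive.
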